### Sample Size

The sample size is based on the number of observations needed to compare the 2 groups of gamers, those trained with Lumosity and those trained with The Sims. As we do not have standard deviations of the scores in our main dependent variables, we used G*Power 3.1 (Department of Psychology) to compute the number of participants, using analysis of variance as a statistical test. For this, using a power of .80, effect size of 0.50, an alpha level of .05, and 2 groups within the *F* test family, we obtained a required total sample size of 57. With a dropout rate of 10%, a total of 63 participants would be required. Rounding up the numbers, we would need more than 64 participants (32×2). As the flow diagram shows, the final number of participants matches these a priori computations closely: 38 participants were assigned to the experimental group (8 lost at posttest) and 37 to the control group (12 lost at posttest).

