### Primary Outcomes

#### Effects of Video Game Training on Attentional Networks: Behavioral and Electrophysiological Results

##### Oddball Task

The capacity to suppress irrelevant information and to concentrate on the relevant task [86] is negatively affected by aging. The question is whether the effects of training with cognitive video games are transferable to untrained tasks (transfer effect). Despite the great appeal of video games as a way to improve perceptual and cognitive abilities, evidence of their efficacy is mixed [49,50,52,64,87-88]. However, the results of several recent meta-analytic studies [59-62] suggest that video game training can be moderately effective in healthy older adults but that its positive effects are moderated by several variables including the complexity of the games, the age of the participants, the duration of the training program, and the cognitive processes assessed.

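### The required total of 57 does not follow from the stated inputs (they give 34 or 128), and the 55 participants left at posttest fall below it, so the claimed close match holds only for the number assigned

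*Protocol article*

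**What the plan says.** The Sample Size section of the protocol article explains that no standard deviations were available for the main dependent variables, so a standardised effect was entered in G*Power 3.1, "using analysis of variance as a statistical test". The inputs are given as "using a power of .80, effect size of 0.50, an alpha level of .05, and 2 groups within the" F-test family. The result is "we obtained a required total sample size of 57". A 10% dropout allowance takes this to 63, which is then rounded up to 64 (32 per arm).

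The section closes by saying that "the final number of participants matches these a priori computations closely: 38 participants were assigned to the experimental group (8 lost at posttest"), with 37 assigned to the control group, of whom 12 were lost at posttest.

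The article does not say whether 0.50 is Cohen's f or Cohen's d, and it gives no numerator degrees of freedom. General Procedure names the interaction of group with testing session (three sessions) as the main question. The Results section plans analyses of variance with two groups at three time points.

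**The concern.** The article prints the inputs, the answer and a conclusion about the answer, and the three do not agree. For a two-group F test, the four stated inputs fix the total sample size once the effect-size metric is known. If 57 cannot be recovered under either metric, the 80% power attached to it has no stated basis. If the posttest sample is also below 57, the reassurance in the closing sentence does not extend to the participants who can be analysed. The primary outcomes are defined by better performance at posttest than at pretest, so the posttest count is the relevant one. Readers will use this paragraph to judge how much a non-significant result can tell them.

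**Working it through.** **Inputs (Sample Size section).** Alpha .05; power .80; effect size 0.50; two groups; F test. Assigned 38 and 37; lost at posttest 8 and 12.

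**Method.** Noncentral F, as G*Power uses for analysis of variance: noncentrality λ = f²N, numerator degrees of freedom df1, denominator N − 2. For two equal groups f = d/2.

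**Step 1: try to reproduce 57.** The stated comparison is between two groups, so df1 = 1.

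| Reading of 0.50 | f | df1 | N for 80% power | Power at that N |
|---|---|---|---|---|
| Cohen's f | 0.50 | 1 | 34 | .807 |
| Cohen's d | 0.25 | 1 | 128 | .801 |
| Cohen's f, group-by-session df | 0.50 | 2 | 42 | .804 |
| Cohen's f, df1 = 5 | 0.50 | 5 | 57 | .803 |

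With f = 0.50 and df1 = 5, N = 56 gives power .794 and N = 57 gives .803, so that setting yields exactly 57. A two-group comparison has 2 − 1 = 1 degree of freedom. The group-by-session interaction has (2 − 1)(3 − 1) = 2. Neither is 5.

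Other settings were tried and also miss 57. Power .95 with f = 0.50 gives 54. One-sided d = 0.50 gives about 102. Repeated-measures tests with f = 0.50 and two groups give 5 to 41, depending on the correlation and the noncentrality convention. With df1 = 1, N = 57 has 80% power at f = 0.378, that is d = 0.755.

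**Step 2: dropout allowance.** 57/0.9 = 63.3, which rounds up to 64; 57 × 1.1 = 62.7, which rounds to 63. Since the article goes on to 64, this is only a rounding matter.

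**Step 3: the sample at posttest.**
- Experimental: 38 − 8 = 30 (8/38 = 21.1% lost)
- Control: 37 − 12 = 25 (12/37 = 32.4% lost)
- Total: 75 − 20 = 55 (20/75 = 26.7% lost, against 10% planned)

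So 75 exceeds 64, but 55 is below 57, before any loss between posttest and the 6-month follow-up.

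**Step 4: power at 30 versus 25.** For an unadjusted two-sided posttest comparison, λ = d² × (30 × 25)/55 = 13.64 d², with df 1 and 53.
- 0.50 is f (d = 1.0): λ = 13.64, power 95.2%
- 0.50 is d: λ = 3.41, power 44.2%
- 80% power is reached at d = 0.77

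**Step 5: the planned repeated-measures test.** Its power depends on the pre-post correlation ρ, which the article does not give. For the pre-to-post change contrast, with d in units of the posttest standard deviation, the detectable effect is 0.773 × √(2(1 − ρ)). Assuming ρ = 0.5 this is 0.77; assuming ρ = 0.7 it is 0.60.

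**The case against.** Four points can be made in defence, and parts of them stand.

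First, 57 can be reached in G*Power with an extra setting, so the fault might be incomplete reporting in a condensed article. That 57 is reachable is true. However, the setting needed is inferred, and it contradicts the two-group comparison that the section says the number is for. An article may leave detail to a fuller document, but here it prints inputs and a result that disagree.

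Second, the closing sentence can be read as being about the number assigned. On that reading it is fair, since 75 exceeds 64, and the losses are disclosed in the same sentence. But 57 was the number required after dropout, and 55 is the figure to set beside it. The shortfall is only two people. Under the df1 = 5 setting, power falls from 80.3% to 78.4%.

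Third, the abstract says that posttest evaluations were still under way, so 55 is the number not reported as lost and might still change.

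Fourth, a reader might infer that the trial has 44% power rather than 80% for a moderate effect. The article does not support this as a flat statement. The Sample Size section never calls 0.50 moderate and never claims 80% power for d = 0.5. In the F-test family that it names, the effect-size entry is f, and on that reading 55 participants give about 95%. The remark in the Oddball Task section that meta-analyses "suggest that video game training can be moderately effective in healthy older adults" is background: it gives no effect size and is not an input to the calculation. The 44% also belongs to an unadjusted posttest comparison, not to the planned group-by-session analysis. Smaller detectable effects based on pretest-adjusted analysis of covariance should not be offered either, because the article does not plan that analysis.

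**Conclusion.** The sample-size statement is wrong as written. From the printed inputs, the required total is 34 if 0.50 is f or 128 if it is d; 57 lies well away from both. The agreement claimed in the closing sentence holds for the number assigned (75 against 64) but not for the sample at posttest (55 against 57, with 26.7% lost against 10% planned).

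The 80% power figure is not supported on either reading of 0.50: in an unadjusted two-sided posttest comparison of 30 and 25 it is about 95% for f and about 44% for d. Which applies cannot be settled from the article, and the choice changes what a null result would mean.

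The required totals rest only on the stated inputs and a two-group F test. The power figures further assume that comparison and the losses as reported. Any figure for the planned interaction needs an assumed pre-post correlation.

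**What to change.** Keep enrolment as it is and rewrite the Sample Size paragraph.

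1. Say whether 0.50 is Cohen's f or Cohen's d, and give the numerator degrees of freedom of the test that the calculation is for.
2. Replace 57 with the total that matches: for the two-group comparison, 34 (f) or 128 (d). If another setting produced 57, state it and say why it fits the planned analysis.
3. Replace the claim of close agreement with the facts: 75 assigned, 55 remaining at posttest, 27% loss against 10% planned, and below the 57 that was calculated. Update the count if posttest assessment is not finished.
4. State the effect detectable with 80% power at 30 versus 25: d about 0.77 for an unadjusted posttest comparison. If a figure is given for the planned group-by-session test, show it as depending on an assumed pre-post correlation (for the pre-to-post change contrast, d about 0.77 at 0.5 and about 0.60 at 0.7).

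The cost is one paragraph of rewording, with no new participants and no change to the analysis. The downside is that the stated figure becomes less favourable.

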### Participants

Participants were randomly assigned to 1 of the 2 parallel groups, either the intervention video game training group or the active control group (see Figure 1). The pretest, posttest, and 6-month follow-up assessments are conducted at the UNED Department of Basic Psychology II by one of the authors with the assistence of other members of the group. The training sessions were carried out at the UNED Associate Center, Escuelas Pías, Madrid, and lasted 8 to 10 weeks. A total of 138 participants were recruited from flyers, advertisements, by word of mouth, and from UNED’s special program for the elderly screened for eligibility. Finally, 75 older adults (age range 55 to 84 years) met the requirements for participation in the study and signed the consent form and were randomly assigned to the experimental or the active control groups before carrying out the laboratory tasks. The 2 groups do not differ significantly in age, years of education, global cognition, depression, memory, or verbal abilities.

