## Methods

### Overview of the Study Design

A 2-arm, parallel-design RCT [72] was designed to evaluate the effectiveness of video game training to promote cognitive and brain health in older adults. Figure 1 shows the Consolidated Standards of Reporting Trials flow diagram of the study. This RCT is being conducted in Madrid, Spain, with an allocation ratio of 1:1 to evaluate the influence of training with nonaction video games on attention and memory functions. The design was a single-blind design. Eligible participants were randomized using a computer algorithm into intervention (cognitive nonaction video game training) or active control (life-simulation games) groups. Researchers were not blind to treatment allocation. The Universidad Nacional de Educación a Distancia (UNED) Institutional Review Board approved the study protocol. All participants provided written informed consent.

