
### General Procedure

Participants in the study were randomly assigned to the cognitive nonaction video game training group or the noncognitive game training active control group. The introduction of an active control group is necessary to avoid placebo effects [54]. Based on the results of our meta-analytic study [61], we use training regimes that are not too long to avoid loss of motivation, and simple, nonaction games that appeal more to elders. According to the temporal discount hypothesis [85], future rewards are less valuable than inmediate rewards. In each session, the trainees play 10 nonaction video games from Lumosity, described below.

The main question examined in our study is whether group (experimental group, active control group) interacts with testing session (pretest, posttest, and follow-up) with regard to performance on a series of cognitive tasks. At least 2 measures for each cognitive domain are acquired to examine transfer of training to untrained tasks demanding attention and working memory. We selected these cognitive domains because these functions deteriorate with aging and tax functions that are critical for independent living. To explore the underlying neural mechanisms of successful transfer of training gains to attentional mechanisms (alert, distraction, and inhibitory effects) and executive control (spatial working memory), electrophysiological data (ERPs) are recorded at pretraining (T1), posttraining (T2), and 6-month follow-up (T3).

All the methodological designs of the primary outcome measures have been constructed using the rules of counterbalancing and stimulus rotation. Response keys are counterbalanced across conditions. The computerized tasks have been programmed using E-Prime 2.0 (Psychology Software Tools Inc). All the statistical analyses of the behavioral results will be performed using SPSS (IBM Corp) and results will be considered significant at *P*<.05, with Bonferroni-corrected post hoc tests performed as appropriate. Continuous EEG activity are recorded in our laboratory with thin electrodes from 34 scalp sites using a NuAmps amplifier as mentioned before.

After randomization and initial assessment (baseline), participants were invited to attend the University Center of Escuelas Pias in Madrid to perform the training sessions in small groups. Trained and active control groups followed 16 training sessions carried out on different hours and days that lasted approximately 10 to 12 weeks.

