##### Assessing Working Memory Updating

Transfer to working memory after training is assessed with the *n*-back task [107]. We use a computerized version of the task to assess memory updating. In this task, participants indicate whether each visual stimulus in a list matches a stimulus that occurred 1, 2, or 3 stimuli back by pressing a response key with their right hand (counterbalancing index and middle fingers to respond “yes” and “no”).

In sum, the primary outcome measures of this RCT are better performance at posttest than at pretest on a series of tasks: (1) Stroop-negative priming task, (b) oddball task, (3) *n*-back task, and (4) Corsi blocks.

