## Results

All analyses will be performed with the SPSS (IBM Corp) program. Statistical significance is considered as a *P* value of <.05. Analyses of variance will be conducted with 2 groups (experimental and active control) at 3 time points (pretest [baseline], posttest [postintervention], and follow-up [after 6 months without contact]). Electrophysiological data will be analyzed using EEGLAB/ERPLAB.

The preparatory phase for using the games has been completed. License to use the games has been granted by Lumosity. Participants have been recruited, pretested, and trained. The final results from this RCT are expected by the end of 2017.

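### The pretest that anchors all four primary outcomes is a post-randomisation measurement, and no stated safeguard keeps the tester unaware of the arm

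*Protocol article*

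**What the plan says.** **Order.** The Participants section states that the 75 eligible, consenting adults "were randomly assigned to the experimental or the active control groups before carrying out the laboratory tasks". General Procedure has a related sentence: "After randomization and initial assessment (baseline), participants were invited to attend" the training centre. That sentence puts both events before training but does not by itself say which came first. The order rests on the Participants section.

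**Who knew.** Overview of the Study Design calls the trial single-blind and adds: "Researchers were not blind to treatment allocation".

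**Who tested.** Participants says: "The pretest, posttest, and 6-month follow-up assessments are conducted at the UNED Department of Basic Psychology II by one of the authors", assisted by other members of the group. One team therefore covers all three sessions.

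**What depends on T1.** The section Assessing Working Memory Updating closes by defining the primary outcomes (Stroop-negative priming, oddball, n-back, Corsi blocks) as "better performance at posttest than at pretest on a series of tasks". General Procedure gives the main question as "whether group (experimental group, active control group) interacts with testing session (pretest, posttest, and follow-up". The Results section sets the model: "Analyses of variance will be conducted with 2 groups (experimental and active control) at 3 time points".

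**The concern.** A baseline is safest when it is fixed before anyone can know the arm. Here the primary tasks were first administered after assignment, by a team described without exception as unblinded. If a tester explains a task more fully to one arm, encourages it more, or treats its written answers differently, the recorded T1 score can move by arm although true ability does not. A T1 score that is too low in one arm looks like a larger training gain at T2 and T3.

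This differs from the familiar weakness of unblinded testing after treatment. There, bias enters at the end of the comparison. Here it can also enter at the starting point, which an analysis of change takes at face value.

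**Working it through.** The article gives no figure on this point. Its only design calculation, a total of 57 in Sample Size, does not enter the argument.

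**Step 1. Is T1 after allocation, and could the tester know the arm?** Participants puts assignment before the laboratory tasks. Overview of the Study Design says the researchers are unblinded, and Participants makes an author the tester. Nothing in the article places the pretest before allocation, conceals allocation until T1 is complete, or describes a blinded assessor. The timing is stated outright. That the T1 tester actually held the allocation is likely but not stated.

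**Step 2. How does a T1 shift reach the result?** Let the differential shift (experimental minus control, in SD units) be δ1 at T1 and δ2 at T2. The group by session contrast from T1 to T2 is

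(T2 − T1) experimental − (T2 − T1) control,

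so its bias is δ2 − δ1.

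- Shift only at T1 (δ1 = −b, δ2 = 0): bias = +b, the full amount.
- Same shift at both sessions (δ2 = δ1): bias = 0.
- Half repeated (δ1 = −b, δ2 = −b/2): bias = b/2.

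The same holds with T3 in place of T2.

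**Step 3. Illustration of size.** Inputs:

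- Completers at T2, from Sample Size: 38 − 8 = 30 and 37 − 12 = 25.
- T1-only shift b: assumed, 0.1 to 0.2 SD. The article gives no value.
- T1–T2 correlation ρ: assumed, 0.5, with a range of 0.3 to 0.7. The article gives no value.
- Two-sided 5% test of the T1-to-T2 change contrast, df = 30 + 25 − 2 = 53. This is the single contrast, not the omnibus test over three sessions.

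The SD of a change score is √(2(1 − ρ)) = √(2 × 0.5) = 1.00. The standard error is 1.00 × √(1/30 + 1/25) = √0.0733 = 0.271. The noncentrality is b/0.271, which is 0.37 at b = 0.1 and 0.74 at b = 0.2.

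Probability of a significant result with no true training effect (noncentral t):

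| b (SD) | ρ = 0.3 | ρ = 0.5 | ρ = 0.7 |
|---|---|---|---|
| 0 | 5% | 5% | 5% |
| 0.1 | 6.1% | 6.5% | 7.5% |
| 0.2 | 9.4% | 11.2% | 15.5% |

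If half of a 0.2 SD shift recurs at T2, the net bias is 0.1 SD and the 0.1 row applies.

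**The case against.** The strongest reply is that the exposure is narrow and the harm conjectural, and much of this stands. The tasks run in E-Prime with counterbalanced keys, which leaves little to the tester beyond instructions and encouragement. Corsi answers are written down by the participant and scored as a proportion correct, so only the handling of the sheets is open. Since the researchers are the unblinded party, single-blind implies that participants did not know their arm, so participants' own effort is a weak route. The same team tests at every session, so a steady habit of encouraging one arm would cancel. These points limit the size of the risk. They do not supply a safeguard at T1.

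The reported similarity of the groups does not settle the matter either. It covers age, education, global cognition, depression, memory and verbal abilities, and does not name the four primary tasks at T1.

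The article does not support several stronger readings that a reader might infer:

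- *Biased baselines have been shown.* The article shows an opening for bias, not its occurrence or direction.
- *Randomisation no longer protects T1.* Allocation still balances true ability. Only its measurement could differ.
- *The bias is 20% to 40% of the planned effect.* This divides an assumed 0.1 to 0.2 SD by 0.50 read as a standardised mean difference. Read as Cohen's f with two equal groups, 0.50 corresponds to a difference of 1.0 SD and the share is 10% to 20%. The article does not say which is meant.
- *Salivary C-reactive protein and early withdrawals are affected too.* The former is a laboratory assay and not a primary outcome. No withdrawal between assignment and pretest is reported in the text.

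**Conclusion.** The point holds as a moderate design weakness. The reference measurement for all four primary outcomes was taken after randomisation, and nothing stated kept the tester unaware of the arm. The timing rests on an explicit statement. That testers knew the arm is inferred from the general statement that researchers were unblinded, and the authors can confirm or correct it.

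The size cannot be estimated from the article. Under the assumed T1-only shift of 0.1 to 0.2 SD, the 5% error of the T1-to-T2 contrast becomes about 6.5% to 11% at a correlation of 0.5, and 6.1% to 15.5% over correlations of 0.3 to 0.7. A shift that recurs equally at T2 and T3 adds nothing.

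**What to change.** The abstract and the Results section show that pretests are complete, posttests are under way and analysis is still to come. The order of pretest and allocation can no longer be changed and should not be redescribed. What can still be done:

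1. Describe T1 as a post-randomisation baseline, and state whether the T1 testers knew the arm. If they did not, correct the blinding statement accordingly.
2. Score all Corsi response sheets from T1, T2 and T3 under a code that hides arm and session.
3. For the remaining T2 visits and all T3 visits, have testing done by existing team members who did not run that participant's training, using a fixed instruction script. They may still learn the arm, so this reduces the risk without removing it.
4. Optionally, and as supportive only, compare the arms at T2 and T3 with adjustment for the pre-randomisation screening scores, age and education in place of T1. This avoids reliance on T1. It is less precise, partly because eligibility restricts the range of the Mini-Mental State and depression scores, and it does not remove bias from unblinded testing at T2 and T3.

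The cost is a small scheduling and coding burden, with no new visits, plus a little extra analysis if item 4 is taken up.

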Two challenges must be overcome in order to develop an effective cognitive aging intervention [54-55]: (1) transferring training gains to untrained tasks and (2) designing interventions that encourage compliance. Older adults prefer games that involve mental challenge [56-57], while studies with young adults have shown that fast-paced action games result in broader transfer effects. A “first-person shooter” video game is not an appropriate choice for older adults [58]. Nonaction video games have potential advantages as they are enjoyable, low-cost, and can be self-administered. Recent results from a systematic review [53] and meta-analyses [59-61] suggest that training elders with video games improves information processing, with unexpected larger effects in old-older adults than in young-older adults. Moreover, the results of a recent meta-analysis of action video game training showed that healthy adults benefit from training in overall and specific cognitive domains, but young adults benefit more than older adults [62]. These findings underscore the potential of video game training as an effective intervention tool for cognitive improvement. Results of studies on executive function and working memory are less consistent. It is possible that nonaction video games are not an effective means of improving or maintaining these functions in older adults. Games provide an enjoyable way of passing the time and of giving meaning to the day [56]. In short, video games can offer important benefits to older adults, bearing in mind that intervention compliance is a key factor in longitudinal training studies [54].

A previous RCT conducted in our laboratory investigated the effects of nonaction video game training on a series of cognitive functions that decline with age and subjective well-being. Two groups of older adults participated in the study: an experimental group that received the training and a noncontact control group. Groups were similar at baseline on demographics, vocabulary, global cognition, and depression status. The results showed improvements in the video game–trained group and no change in the passive control group in processing speed, attention, and immediate and delayed visual recognition memory and a trend to improve in 2 dimensions of the Well-being Scale (affection and assertivity) [63]. However, visuospatial working memory and executive control (shifting strategy) functions did not improve [49,64,65].

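### The main group-by-session analysis has no age term although the protocol says training gains vary with age; prespecifying baseline age and its interaction with session would be a small, nearly free gain in precision

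*Protocol article*

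**What the plan says.** **Age as a moderator.** The Background section reports from a systematic review and meta-analyses that video game training improves information processing in older people, "with unexpected larger effects in old-older adults than in young-older adults". It adds that, for action games, young adults gained more than older adults. The Oddball Task section says of training that "its positive effects are moderated by several variables including the complexity of the games, the age of the participants", among other variables.

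**Age in the sample.** The Eligibility and Exclusion Criteria section lists no age limit. The Participants section gives the achieved range, 55 to 84 years, for the 75 randomised, and adds: "The 2 groups do not differ significantly in age, years of education, global cognition, depression, memory, or verbal abilities".

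**Age in the analysis.** General Procedure frames the main question as the interaction of group with testing session. The Results section states the model: "Analyses of variance will be conducted with 2 groups (experimental and active control) at 3 time points". Neither section names age. The one exception is in the Stroop and Negative Priming Task section, where the design for the negative priming effect includes a factor contrasting younger with older adults, next to session and type of intervention.

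**The concern.** The article gives its own reason to expect change from pretest to vary with age, and the sample spans about 30 years of age. A model with group and session alone leaves any such variation in the error term. At the numbers remaining at posttest, it also leaves any chance difference in age between the arms inside the estimated training effect. Age is already recorded, so the loss can be avoided.

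The negative priming design raises a second, separate question. It uses an age-group factor that the main model lacks, and the article describes no younger cohort. A reader cannot tell whether age groups are to be compared in that analysis or whether the factor does not belong to this trial.

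**Working it through.** The plan gives no figure on this point to reproduce; its sample size calculation contains no age term and does not bear on it.

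**Inputs from the article.** Sample Size section: 38 and 37 randomised, 8 and 12 lost at posttest, so 30 and 25 remain. Loss is 8/38 = 21.1% and 12/37 = 32.4%.

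**Assumptions, not in the article.** Age SD of 6 to 8 years; correlation *r* between age and change of 0.2 to 0.4; a treatment effect of 0.5 SD of change, for illustration.

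**1. Precision gained.** Adjustment multiplies residual variance by 1 − *r*².
- *r* = 0.2: 1 − 0.04 = 0.96, so 4% is removed.
- *r* = 0.4: 1 − 0.16 = 0.84, so 16% is removed.
- The standard error falls by the square root: √0.96 = 0.98 and √0.84 = 0.92, so confidence intervals are about 2% to 8% narrower.
- Two-sided 5% test at 30 versus 25, effect 0.5 SD: power is 44% unadjusted, 46% at *r* = 0.2, 48% at *r* = 0.3 and 51% at *r* = 0.4 (noncentral *t*, effect divided by √(1 − *r*²)).
- Cost: error degrees of freedom per session contrast go from 55 − 2 = 53 to 52.

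**2. Chance imbalance at posttest.** The 95% chance range for the difference in mean age is ±1.96 × SD × √(1/30 + 1/25) = ±0.531 × SD, using √0.0733 = 0.271.
- Age SD 6, 7 and 8: ±3.2, ±3.7 and ±4.2 years.
- An imbalance at that limit shifts the unadjusted difference in change by *r* × 0.531, which is 0.11 SD at *r* = 0.2 and 0.21 SD at *r* = 0.4.

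**3. What the baseline sentence can show.** At 38 versus 37, differences up to about 1.96 × SD × √(1/38 + 1/37) = 0.453 × SD stay non-significant: 2.7, 3.2 and 3.6 years for SD 6, 7 and 8. With the exact *t* quantile the limit is 0.46 SD. The test has 25% power for a true difference of 0.3 SD and 40% for 0.4 SD. The sentence is attached to the 75 randomised, not to the 55 remaining.

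**4. Testing moderation.** With an even split by age, the standard error of the age-by-treatment interaction is twice that of the overall difference. At 30 versus 25, power is about 15% if the effect differs by 0.5 SD between age halves, and 44% if it differs by 1.0 SD.

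**5. Sections side by side.** General Procedure and Results: two arms, three sessions, no age factor. Participants: one sample of older adults. Stroop and Negative Priming Task: a younger-versus-older factor. The last does not fit the other two.

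**The case against.** The case against is strong in several parts.

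- *A condensed article may leave covariates to a fuller document.* True, and the missing age limit, stratification factors and baseline table are not findings. What remains is that a model is stated, and that it lacks a variable which the article's own rationale names.
- *A reader might infer that comparability, or the omission of age, rests on the non-significant baseline test.* The text does not say so. It reports the result in one descriptive sentence and builds nothing on it.
- *A reader might infer that the plan ignores age altogether.* That is too broad, because the negative priming design names an age-group factor, however hard it is to place.
- *A reader might infer that the unadjusted comparison is biased.* Under randomisation, chance imbalance is already covered by the test's error rate, so omitting age mainly costs precision. Nothing in the article says that dropout was related to age, and an age covariate would not settle a missing-data problem.
- *Moderation is not confounding.* Also right. A varying effect does not invalidate the average group × session comparison, and age × session does not test moderation.
- *Stable age differences in level cancel in a within-participant comparison.* Correct. The general statements that these functions decline with age therefore carry little weight; only a relation between age and change matters, and the article gives no size for it.
- *The gain is small.* It is, and the working shows it.

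**Conclusion.** The point stands as a small improvement in precision and robustness, not as an error that undermines the trial. The stated main model has no age term, while the protocol describes training gains as varying with age and randomised a wide age range. Adjustment would remove about 4% to 16% of residual variance and raise illustrative power from 44% to between 46% and 51%. It would also take out a possible shift of up to about 0.11 to 0.21 SD from chance age imbalance at posttest. All of these sizes depend on an assumed correlation of 0.2 to 0.4 between age and change; near zero correlation the benefit vanishes. The loss of 21% versus 32% remains an open matter whatever is done about age. The negative priming factor is an inconsistency in its own right and needs no assumption.

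**What to change.** - In each primary group × session analysis, prespecify baseline age as a continuous, mean-centred covariate together with its interaction with session. The interaction is needed: a main effect of age alone does not touch the within-participant contrast. Centring keeps the session effect interpretable.
- Fix this before outcome data are examined by arm. When the article was written, posttest assessment was under way and analysis was still to come.
- If age moderation is of interest, add an age × group × session term, labelled exploratory.
- Do not offer the baseline non-significance sentence as evidence of balance; in the results report, give age by arm as mean and SD for the 75 randomised and the 55 remaining.
- Reconcile the younger-versus-older factor in the negative priming design with General Procedure and Results: either remove it or state which participants form the younger group.

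The cost is about one degree of freedom per contrast, one variable already collected and a corrected sentence. Handling of the unequal dropout has to be addressed separately.
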